**Methods/Design:**

The PRINCE Trial is a two-armed, single blind cluster randomised trial conducted in the primary care setting in Ireland. Randomisation to control and intervention is at the level of the General Practice. Participants in the intervention arm will receive a SEPRP and those allocated to the control arm will receive usual care. Delivery of the SEPRP will be by a practice nurse and physiotherapist in the General Practice (GP) site. The primary outcome measure of the study will be health status as measured by the Chronic Respiratory Questionnaire (CRQ). Blinded outcome assessment will be undertaken at baseline and at twelve-fourteen weeks after completion of the programme. A comparison of outcomes between the intervention and control sites will be made to examine if differences exist and, if so, to what extent between control and experimental groups. Sample size calculations estimate that 32 practices with a minimum of 10 participants per practice are required, in total, to be randomised to control and intervention arms for power of at least 80% with alpha levels of 0.05, to determine a clinically significant change of 0.5 units in the CRQ. A cost effectiveness analysis will also be conducted.

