## Sample Size Estimation

We used methods for standard sample size estimates for trials that randomised at the level of the individual [30] adjusting for clustering by inflating sample size estimates by the design effect given by $1+(\bar{n}-1)\rho$, where $\bar{n}$ is the average cluster size, and ρ is the estimated intraclass correlation coefficient (ICC) [31]. Sample size estimates are based on the primary outcome of health status as measured by the CRQ [23], expressed as the mean rate difference between intervention and control groups.

Previous work suggests 0.5 as the minimal clinically important mean difference for all four dimensions of the CRQ [32] and estimates of standard deviations of 1.145 (given as arithmetic mean of 0.88, 1.06, 1.24 and 1.40 for the Dyspnoea, Fatigue, Emotion and Mastery dimensions of the CRQ respectively) [33]. Using these values and the upper value of 0.05 from a range of ICC values identified within studies involving the older person in primary care, [34] calculations indicate that 32 practices with a minimum of 10 participants per practice are required, in total, to be randomised to control and intervention arms for power of at least 80% with alpha levels of 0.05. This allows for participant loss to follow-up of 20% plus a loss of 4 practices. ICC values lower than 0.05 would increase the power of the study.

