## Quantitative Analysis

The analysis will be based on the GP Practice with the patient as the unit of analysis whilst accounting for the intracluster correlation coefficient. Analyses will be by intention to treat. Quantitative data will be analysed, in aggregate, using The Statistical Package for the Social Sciences (SPSS, v17) and R ([37], 2.11). Data will be entered into SPSS, coded, cleaned and locked before any analyses are made. Only members of the research team who needed access to the database to fulfil their roles within the study were granted access to the database. Funders did not have access to the database at any time. Demographic characteristics of the practices and the participants within the practices will be described using percentages, measure of central tendency (means or medians) and measures of variation (standard deviations or ranges). Comparability of randomised groups by socioeconomic and other categorical baseline variables will be by the chi-square (*X*^2^) test.

Whilst every effort will be made to exclude all confounders at the design phase of the study, this is not always possible. The analysis of data will therefore include the search for and control of nuisance variables for which adjustments had not been made. In particular, a mixed effects model will be used to model the longitudinal change in the mean scores for each of the four dimensions of the CRQ primary response while adjusting for explanatory variables and baseline CRQ as needed and incorporating random effects to model the homogeneity within cluster and the correlation within patient across time. The Akaike information criterion (AIC), for linear mixed-effects models in the analysis of clustered data, will be used to decide between candidate models [38]. The significance level will be set at α = 0.05 for all analyses.

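### The stated power of at least 80% after losing 20% of patients and 4 practices leaves no room for the small number of practices: on practice-level degrees of freedom it is about 77%

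*Protocol article*

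**What the plan says.** The Sample Size Estimation section of the protocol article names its method: "We used methods for standard sample size estimates for trials that randomised at the level of the individual", inflated by a design effect of one plus (average cluster size minus one) times the intraclass correlation (ICC).

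Its inputs are:
- a difference of "0.5 as the minimal clinically important mean difference for all four dimensions" of the CRQ;
- "estimates of standard deviations of 1.145", the average of four domain values;
- "the upper value of 0.05 from a range of ICC values" found in other primary care studies.

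The result is 32 practices in total, with at least 10 participants each, for "power of at least 80% with alpha levels of 0.05". The section then says of this result: "This allows for participant loss to follow-up of 20% plus a loss of 4 practices". The Abstract repeats the 32 practices, "for power of at least 80% with alpha levels of 0.05, to determine a clinically significant change of 0.5 units in the CRQ".

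The Randomisation section allocates whole practices 1:1. The Quantitative Analysis section plans a mixed model with random effects for practice and patient, adjusted for baseline CRQ as needed, and says: "The significance level will be set at α = 0.05 for all analyses". It does not state the reference distribution for the arm effect.

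**The concern.** The design effect corrects the variance of the arm difference for clustering. It does not correct for the fact that the between-practice variance must be estimated from a small number of practices. With 28 practices in two arms there are 26 degrees of freedom, and the two-sided 5% critical value is 2.056, not 1.960.

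The section says that the 80% already includes the two losses. If the 80% was reached with the normal critical value and no reserve, a test that keeps the 5% level has less than the stated power in the very scenario that the sentence covers.

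**Working it through.** **Inputs (Sample Size Estimation).** Difference 0.5; SD 1.145; ICC 0.05; alpha 0.05; power 80%; 32 practices of 10; 20% patient loss (10 becomes 8 per practice); 4 practices lost (32 becomes 28, or 14 per arm if even). The section does not say whether alpha is two-sided. Two-sided is taken here because a one-sided alpha gives 11 practices per arm, so 22 + 4 = 26, not 32.

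**Step 1: reproduce the plan's figure.**
- Individual-level n per arm = 2 × (1.960 + 0.842)² × 1.145² / 0.5² = 82.3.
- Design effect at 8 analysed per practice = 1 + 7 × 0.05 = 1.35.
- 82.3 × 1.35 = 111.1 patients per arm; 111.1 / 8 = 13.9, so 14 practices per arm, or 28.
- 28 + 4 = 32, as stated.

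Other routes miss 32. Rounding 82.3 up to 83 before inflating gives 83 × 1.35 / 8 = 14.01, so 15 per arm and 30 + 4 = 34. A calculation on practice-level degrees of freedom also needs 15 per arm (step 3), so again 34. The normal critical value is therefore inferred from the match; the section does not name it.

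**Step 2: power with the normal critical value, 14 practices of 8 per arm.**
- Standard error = √(2 × 1.145² × 1.35 / 112) = 0.1778.
- Noncentrality = 0.5 / 0.1778 = 2.812.
- Power = Φ(2.812 − 1.960) = 80.3%.

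The reserve above 80% is 0.3 points.

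**Step 3: the same inputs on practice-level degrees of freedom.** The noncentrality is computed as in step 2, and power comes from the noncentral t distribution with (practices − 2) degrees of freedom.

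| Practices analysed (8 patients each) | Degrees of freedom | Power, normal | Power, t |
|---|---|---|---|
| 16 + 16 (none lost) | 30 | 85.2% | 82.9% |
| 15 + 15 (2 lost) | 28 | 82.9% | 80.2% |
| 14 + 14 (4 lost, even) | 26 | 80.3% | 77.3% |
| 12 + 16 (4 lost, one arm) | 26 | 79.5% | 76.4% |

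In the last row the normal calculation also falls below 80%.

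**Step 4: where the shortfall arises.** On the t basis, 32 practices of 10 with no loss give 88.1%. Practice loss alone (28 of 10) gives 83.2%, and patient loss alone (32 of 8) gives 82.9%. Power is below 80% when the two stated losses are combined in full.

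**Step 5: conditional type I error.** If the arm effect were compared with 1.960 when its statistic follows t on 26 degrees of freedom, the two-sided error rate would be P(|t₂₆| > 1.960) = 6.1%.

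**The case against.** The strongest reply is that the section states its method openly and applies it correctly, so there is no slip in the sums. That stands: the issue is what the approximation leaves out, not how it was computed.

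A second reply is that the plan has margins that the 77% ignores. With 28 practices and t on 26 degrees of freedom:
- 9 analysed patients per practice instead of 8 give 80.5%, and 10 is a minimum practice size;
- an ICC of 0.04 gives 79.4%, and 0.03 gives 81.6%; the section itself says that lower values would raise power;
- if 1.145 is the SD of raw follow-up scores (an assumption; the section does not say), adjusting for a baseline that correlates 0.2 with outcome gives 78.9%, 0.3 gives 81.0% and 0.5 gives 87.8%.

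These offsets are plausible and soften the point. They do not remove it, because the stated figure is made at ICC 0.05 and at the minimum practice size, gives no baseline correlation, and adjusts for baseline only as needed.

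Two stronger readings should be resisted. A reader might infer that the trial's real false-positive rate is 6%. The article does not support that: it sets alpha at 0.05 and names no reference distribution for the mixed model, a detail that can properly sit in an analysis plan that is not shown. A reader might also infer that the losses are not allowed for at all. They largely are: the allowance absorbs all but about 3 points.

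**Conclusion.** The statement of at least 80% power at alpha 0.05 after both losses does not hold on the plan's own inputs once the number of practices is taken into account. Power is 77.3% with 28 practices of 8, and 76.4% if the four lost practices are all in one arm. On this basis 80% survives the loss of 2 practices, not 4.

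The shortfall is small, about 3 points. It rests on a two-sided 5% test, difference 0.5, SD 1.145, ICC 0.05, equal practices of 8 analysed patients and no baseline adjustment. It also rests on the inference that a normal critical value was used, which the exact match to 32 supports. It does not depend on whether averaging the four domain SDs was sound, since 1.145 is kept throughout. The 6.1% error rate applies only if the analysis uses a normal reference.

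**What to change.** In the Abstract and in Sample Size Estimation, restate planning power with 20% patient loss as about 83% with no practice lost, 80% with 2 lost and 77% with 4 lost, for an unadjusted comparison at ICC 0.05 and SD 1.145.

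In the mixed model, test the arm effect on practice-level degrees of freedom (practices minus 2, or Satterthwaite or Kenward-Roger), so that the 5% level is kept. If the analysis plan already says this, a reference to it is enough.

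The cost is about two sentences and a slightly less favourable stated power. No extra practices or patients are needed.

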## Randomisation

### Random allocation sequence generation

Randomisation is at the level of the general practice (cluster). The random allocation sequence will be generated using a computer generated random number list [35]. To minimise the time delay between practices agreeing to participate and the commencement of the training programme for practice nurses and the implementation of the intervention for experimental clusters and patients therein, practices will be randomised in blocks of clusters when all patient participants in the block of clusters have been recruited. We propose to randomise clusters in four groups of clusters on a 1:1 ratio. This approach is recognised as a legitimate means of overcoming long delays between recruitment and implementation of the intervention in cluster trials [36].

### Allocation concealment

Concealment of group allocation will be achieved by giving the responsibility for allocation sequence generation and group allocation to a researcher independent of the study and its investigators.

### Implementation

The research team will provide the independent researcher with a list of the first group of participating practices that meet the eligibility criteria and consent to participate. The independent researcher will then (i) consecutively number all participating practices in this group (ii) generate the random allocation sequence as detailed (iii) assign practice to group allocation and (iv) notify the PRINCE Project Manager of the practice allocations. The same allocation procedure will be followed for subsequent groups.

### Blinding

Patient participants within each participating practice will be recruited prior to random allocation of practices to control and intervention groups. Because of the nature of the intervention, it is not possible to blind participants (GP Practices or clients) to practice group allocation. Outcome assessment will be blinded to group allocation by (i) blinding Research Assistants responsible for outcome assessment to the group allocation of participating practices and patients with any exceptions recorded and (ii) having data analysis performed by researchers and statisticians blinded to group allocation by providing database of outcomes with groups identified numerically only.

## Quantitative Analysis

The analysis will be based on the GP Practice with the patient as the unit of analysis whilst accounting for the intracluster correlation coefficient. Analyses will be by intention to treat. Quantitative data will be analysed, in aggregate, using The Statistical Package for the Social Sciences (SPSS, v17) and R ([37], 2.11). Data will be entered into SPSS, coded, cleaned and locked before any analyses are made. Only members of the research team who needed access to the database to fulfil their roles within the study were granted access to the database. Funders did not have access to the database at any time. Demographic characteristics of the practices and the participants within the practices will be described using percentages, measure of central tendency (means or medians) and measures of variation (standard deviations or ranges). Comparability of randomised groups by socioeconomic and other categorical baseline variables will be by the chi-square (*X*^2^) test.

Whilst every effort will be made to exclude all confounders at the design phase of the study, this is not always possible. The analysis of data will therefore include the search for and control of nuisance variables for which adjustments had not been made. In particular, a mixed effects model will be used to model the longitudinal change in the mean scores for each of the four dimensions of the CRQ primary response while adjusting for explanatory variables and baseline CRQ as needed and incorporating random effects to model the homogeneity within cluster and the correlation within patient across time. The Akaike information criterion (AIC), for linear mixed-effects models in the analysis of clustered data, will be used to decide between candidate models [38]. The significance level will be set at α = 0.05 for all analyses.

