### Demographic variables

Data will be collected from each patient participant on current medication use, smoking history, education level, marital and employment status, level of social engagement and level of support with activities of daily living.

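### Baseline comparability is to be judged by an ordinary chi-square test that ignores clustering by practice, so its p-values are too small for any variable that varies between practices

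*Protocol article*

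**What the plan says.** The Quantitative Analysis section sets the baseline comparison: "Comparability of randomised groups by socioeconomic and other categorical baseline variables will be by the chi-square" test. No cluster-adjusted form is named. The same section adds: "The significance level will be set at α = 0.05 for all analyses".

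Practices, not patients, are the unit of allocation (Random allocation sequence generation): "We propose to randomise clusters in four groups of clusters on a 1:1 ratio". The Sample Size Estimation section recognises that this matters. It inflates the individual-level sample size by a design effect and takes "the upper value of 0.05 from a range of ICC values identified within studies involving the older person in primary care".

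Two other statements bear on the point. The Quantitative Analysis section opens by saying that patients are the unit of analysis and that the intracluster correlation is accounted for. Its next paragraph says: "The analysis of data will therefore include the search for and control of nuisance variables for which adjustments had not been made". It then describes a mixed model for the CRQ domains with random effects, adjustment as needed, and AIC to choose between candidate models.

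**The concern.** A Pearson chi-square test takes its reference distribution from independent observations. When whole practices are allocated and patients within a practice are alike, the difference in proportions between arms varies more than the test allows for. Chance differences then reach p < 0.05 more often than 5% of the time.

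The test also has little to find. According to the Blinding and Outcome measures sections, patients are recruited and baseline outcomes are taken before practices are allocated. According to Allocation concealment, a researcher independent of the study does the allocating. If this is carried out as written, every baseline difference is due to chance, and a p-value says nothing about whether a difference matters for the outcome.

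Readers use the baseline comparison to judge whether randomising a few dozen practices produced similar arms. P-values that are too small there invite unwarranted claims of imbalance.

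**Working it through.** **Inputs from the article.** At least 10 participants in each of 32 practices, 1:1 allocation, so 16 × 10 = 160 patients per arm at baseline. ICC 0.05, used for sizing on the CRQ. Difference 0.5, SD 1.145, power at least 80%, alpha 0.05, participant loss 20%, and four practices lost.

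**The plan's own figure first.** SD: (0.88 + 1.06 + 1.24 + 1.40)/4 = 1.145. Patients per arm without clustering: 2 × (1.145 × 2.8016/0.5)² = 82.3. With 20% loss, 10 patients become 8, so the design effect is 1 + 7 × 0.05 = 1.35. Practices per arm: 82.3 × 1.35/8 = 13.9, rounded up to 14. In total 28, plus 4 lost, is 32. Power at 14 × 8 per arm is 0.803. The stated 32 is reproduced, which confirms how the plan uses its ICC and design effect.

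**Assumptions for the baseline test.** The ICC of each baseline variable is assumed, because none is given. Practices contribute equal numbers and are allocated at random; the calculation ignores the randomisation in four groups.

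**Binary variable.** With m patients per practice, DE = 1 + (m − 1) × ICC. The true rejection rate of a nominal 5% chi-square on 1 df is 2 × [1 − Φ(1.96/√DE)]. At ICC 0.05 and m = 10, DE = 1.45 and 1.96/√1.45 = 1.63, which gives 0.104.

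| ICC (m = 10) | DE | True rate |
|---|---|---|
| 0.01 | 1.09 | about 6% |
| 0.02 | 1.18 | 7.1% |
| 0.03 | 1.27 | 8.2% |
| 0.05 | 1.45 | 10.4% |
| 0.10 | 1.90 | 15.5% |
| 0.20 | 2.80 | about 24% |

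The rate reaches 10%, twice nominal, when DE = 1.42, that is at ICC (1.42 − 1)/9 = 0.047.

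**Check by simulation.** Beta-binomial data, 2 × 16 practices of 10, 60,000 replicates, ICC 0.05: the unadjusted test rejects 10.6% of the time. With Yates correction it rejects 8.5% to 8.7%. Dividing the chi-square by the design effect brings the rate to 4.8% to 5.0%.

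**Larger practices.** Ten is a minimum. At m = 15 the rate is 10.0% at ICC 0.03 and 13.3% at ICC 0.05.

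**Multi-category variables.** The rate is P(χ² > critical value/DE) on the same degrees of freedom, assuming one ICC across categories. At ICC 0.05 and m = 10 it is 12.7% on 2 df, 14.5% on 3 df and 16.2% on 4 df.

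**The case against.** The best defence is the opening sentence of the Quantitative Analysis section, which promises to account for the intracluster correlation. The article is condensed, so a clustered form of the test could be specified elsewhere. This lowers confidence about what is intended, but it does not change what the named test does. The only method described that handles clustering is the mixed model for the CRQ.

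A second defence is that little follows. This stands: the primary analysis carries random effects for cluster and for patient, so its test does not inherit the error.

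Three stronger readings are tempting, and the article does not support them:

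- A reader might infer that false flags always occur at twice the nominal rate or more. For a binary variable at 10 per practice this needs an ICC of about 0.047. The plan's 0.05 is the upper end of a range and was chosen to size the CRQ outcome. At ICC 0.01 to 0.03 the inflation is 1.2 to 1.6 times.
- A reader might infer that chi-square results pick the adjustment covariates and so alter the primary estimate. No sentence says so, and the stated rule for choosing between models is AIC. The search for nuisance variables comes directly afterwards and does not say how candidate variables are found, so the risk is left open, but it is not a stated rule.
- A reader might compound the error over the seven items under Demographic variables ("current medication use, smoking history, education level, marital and employment status, level of social engagement and level of support" with daily living), or apply it to a practice-level factor such as urban or rural location. The article does not say that all seven are categorical or tested. Seven valid independent tests would already give 1 − 0.95⁷ = 30% for at least one flag. Practice location appears only as a sampling criterion in the qualitative study.

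**Conclusion.** The test named for baseline comparability does not fit the design and is wrong as written. Its p-values are too small at every positive ICC. For a binary variable and 10 patients per practice, the false-flag rate is about 6% to 16% against a nominal 5% over assumed ICCs of 0.01 to 0.10, and 10.4% at the plan's sizing value of 0.05. It is higher for multi-category variables and larger practices. The range rests on assumed ICCs, equal practice sizes and allocation carried out as described.

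The consequence is limited to misleading p-values in the baseline comparison, with an open risk that they influence which variables are adjusted for. The primary model is not invalidated.

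**What to change.** Replace the chi-square sentence with: *Baseline characteristics of practices and patients will be summarised by arm without significance tests.* State that adjustment covariates are chosen on prognostic grounds and not on baseline p-values, which closes the risk left by the nuisance-variable search.

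If a test is wanted as a check on allocation, name one that accounts for practice, for example a chi-square divided by the design effect or a mixed logistic model with practice as a random effect. Even then it would show only whether allocation worked, not which variables matter for the outcome.

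The cost is a sentence or two of text. No new data are needed, and dropping the tests reduces the analysis work.

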## Outcome measures

Outcome measures will be collected from participants in both intervention and control groups at baseline (following consent, prior to randomisation and group allocation) and at 12-14 weeks post completion of the 8-week programme or at an equivalent time for the control group. We acknowledge that a longer follow-up period would be desirable but funding does not permit follow-up beyond this.

Each participating practice will be assigned a Research Assistant responsible for outcome assessment on all participating patients within that practice. To enhance the quality of measurements, all Research Assistants will undergo a one-day Research Assistant Preparation Programme consisting of:

i) Training on the procedures and protocols surrounding the delivery, assessment and recording of all outcome measurements;

ii) Discussion on adverse events and their management;

iii) Simulated completion of all data collection instruments and forms;

iv) Basic Life Support training (for those requiring certification);

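### Baseline CRQ adjustment is conditional, and the covariates and model are chosen after the data are in, so the primary estimate for each CRQ dimension is not fixed in advance

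*Protocol article*

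**What the plan says.** The Quantitative Analysis section sets out the primary analysis in a few sentences. Four features matter here.

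- **Baseline and covariates.** The mixed model is to describe longitudinal change in each of the four CRQ dimensions "while adjusting for explanatory variables and baseline CRQ as needed". No criterion says when adjustment is needed.
- **Covariate search.** The analysis is to include "the search for and control of nuisance variables for which adjustments had not been made".
- **Model choice.** AIC "will be used to decide between candidate models".
- **Clustering.** The model is described as "incorporating random effects to model the homogeneity within cluster and the correlation within patient across time", and the section opens by promising an analysis "with the patient as the unit of analysis whilst accounting for the intracluster correlation coefficient". The condition attached to baseline and covariates is not attached to these random effects.

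Under Outcome measures, the CRQ is collected in both groups before allocation. Under Blinding, the analysts see the groups only as numbers. The Quantitative Analysis section also says that the database is locked before any analysis.

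**The concern.** A confirmatory comparison needs one treatment estimate that is defined before the outcome data are seen. Here the wording covers at least three different primary analyses for each dimension: follow-up score adjusted for baseline, follow-up score alone, and change from baseline without further adjustment. They have different standard errors and can give different answers in the same trial. Nothing in the text requires the four dimensions to end with the same model.

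The baseline score is probably the strongest predictor available and is already planned for every participant. Making it optional puts precision at risk for no return, in a trial whose sample size leaves little spare power.

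AIC also ranks models by expected predictive fit. That is not the purpose of a primary treatment comparison, and in a cluster trial the practice effect has to stay in the model whatever its estimated size.

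**Working it through.** **Inputs.** From Sample Size Estimation: difference 0.5; SD 1.145 (the mean of 0.88, 1.06, 1.24 and 1.40); ICC 0.05, described as the upper value of a range; 32 practices of 10; allowance for 20% participant loss and 4 lost practices; power 80%; alpha 0.05. Assumed: a two-sided test, equal practice sizes, and a baseline–follow-up correlation r that is the same at patient and practice level. The article gives no r, so a range is shown.

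**1. The plan's own figure.** With 10 × 0.8 = 8 completers per practice, the design effect is 1 + 7 × 0.05 = 1.35. Individually randomised n per arm = 2 × (1.145 × (1.960 + 0.842) / 0.5)² = 82.3. Then 82.3 × 1.35 = 111.1, and 111.1 / 8 = 13.9, so 14 practices per arm, 28 in total, plus 4 = 32. The stated number reproduces. Power at 28 × 8 is 80.3% by the normal approximation and 77.3% by a t-test on 26 degrees of freedom. The t-test is used below.

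**2. What baseline is worth.** The follow-up-only SE is 1.145 × √(2 × 1.35 / 112) = 0.178. With baseline as a covariate, multiply by √(1 − r²). For a plain change score, multiply by √(2(1 − r)).

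| r (assumed) | SE, covariate | Power, covariate | SE, change score | Power, change score | Power, follow-up only |
|---|---|---|---|---|---|
| 0.4 | 0.163 | 84.0% | 0.195 | 69.6% | 77.3% |
| 0.5 | 0.154 | 87.8% | 0.178 | 77.3% | 77.3% |
| 0.6 | 0.142 | 92.3% | 0.159 | 85.7% | 77.3% |

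For Mastery alone (SD 1.40), follow-up-only power is 60.1%, and with baseline as a covariate at r = 0.5 it is 72.5%.

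**3. Would AIC drop baseline?** In 1,500 simulated trials (N = 224, r = 0.6, clustering ignored) it never did.

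**4. Does the covariate search inflate type I error?** With six candidate covariates and arm always kept, AIC selection gave 5.1%. Choosing the subset with the smallest treatment p-value gave 9.6%, but the article does not plan that.

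**5. What if AIC also judged the practice effect?** Null trials of 28 × 8 were simulated with maximum-likelihood fits with and without a practice intercept. The intercept was kept only if twice the log-likelihood gain was at least 2.

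| True ICC | Practice effect dropped | Type I error, AIC decides | Type I error, always kept |
|---|---|---|---|
| 0.01 | 92% | 5.5% | 5.0% |
| 0.03 | 82% | 6.5% | 5.0% |
| 0.05 | 67% | 7.0% | 5.0% |

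With REML at ICC 0.05, the effect is dropped in 59% of trials and the error is 6.5%.

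**The case against.** The strongest reply is that the plan is better than a literal reading suggests. Three stronger conclusions are tempting, and the article does not support them.

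- **That AIC may remove the practice effect.** The random effects are incorporated without condition, the section commits to accounting for the ICC, and AIC is introduced for mixed models of clustered data. Dropping practice would conflict with that text. What stands is narrower: the article does not expressly exempt the practice effect from selection. Step 5 shows what would follow if it were not exempt, and 0.05 is the top of the plan's ICC range.
- **That the plan as written loses precision.** A prognostic baseline would almost always survive AIC, and a longitudinal model already uses the baseline data in some form. The loss arises only if baseline is judged unnecessary or if the model reduces to a plain change score. Chance baseline imbalance is not an additional harm, because the unadjusted standard error already includes it.
- **That selection makes the standard errors too small.** For AIC covariate selection, step 4 shows no material inflation. Numeric group labels and database lock further limit steering, although numeric labels do not hide how large the group difference is under each candidate model.

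It is also fair to say that a covariate list and a candidate set are details an article may leave to the full plan. Their absence is not the point. The article states a rule that makes the model depend on the data, and a later plan with one fixed model would have to reverse it.

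**Conclusion.** The concern holds in a limited form. The article makes baseline adjustment conditional and leaves the covariates and model to a search made on the trial data, so the primary estimate is not defined in advance for any of the four dimensions.

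The size depends on which permitted analysis is used. If baseline is omitted rather than made a covariate, about 7 to 15 points of power are lost (84.0 − 77.3 = 6.7 at r = 0.4; 92.3 − 77.3 = 15.0 at r = 0.6). With a plain change score the loss runs from about 14 points at r = 0.4 (84.0 − 69.6) to about 7 at r = 0.6 (92.3 − 85.7). These figures rest on the assumed correlation and on the plan's SD, ICC and attrition. They measure what the wording puts at risk, not a loss that the plan is bound to incur.

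The type I error of about 7% applies only if the practice effect were put to AIC, which the text does not propose. The case for change is that fixing the model is better practice and nearly free, not that the planned test has been shown to be invalid.

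**What to change.** Replace the conditional wording and the AIC sentence with one primary model, the same for all four dimensions: a mixed model with arm, the baseline score of the same CRQ dimension always included, and a practice random effect always kept whatever its estimate. Test arm on degrees of freedom suited to the number of practices. Name any further covariates before unblinding. Move the nuisance-variable search and AIC comparisons to sensitivity analyses, labelled as such.

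The cost is about two sentences. Baseline CRQ collection is already planned for everyone, so no new data, visits or patients are needed.
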